**LIST OF ABBREVIATIONS AND RELEVANT DEFINITIONS**

|                |                                                                                                                                                                                                                                                                                                                                                  |
|----------------|--------------------------------------------------------------------------------------------------------------------------------------------------------------------------------------------------------------------------------------------------------------------------------------------------------------------------------------------------|
| ABR     | ABR form (General Assessment and Registration form) is the application form that is required for submission to the accredited Ethics Committee (ABR = Algemene Beoordeling en Registratie)                                                                                                                                                |
| AE      | Adverse Event                                                                                                                                                                                                                                                                                                                             |
| AR      | Adverse Reaction                                                                                                                                                                                                                                                                                                                          |
| CA      | Competent Authority                                                                                                                                                                                                                                                                                                                       |
| CCMO    | Central Committee on Research Involving Human Subjects                                                                                                                                                                                                                                                                                    |
| CV      | Curriculum Vitae                                                                                                                                                                                                                                                                                                                          |
| DSMB    | Data Safety Monitoring Board                                                                                                                                                                                                                                                                                                              |
| EU      | European Union                                                                                                                                                                                                                                                                                                                            |
| EudraCT | European drug regulatory affairs Clinical Trials GCP Good Clinical Practice                                                                                                                                                                                                                                                               |
| IB      | Investigator's Brochure                                                                                                                                                                                                                                                                                                                   |
| IC      | Informed Consent                                                                                                                                                                                                                                                                                                                          |
| IMP     | Investigational Medicinal Product                                                                                                                                                                                                                                                                                                         |
| IMPD    | Investigational Medicinal Product Dossier                                                                                                                                                                                                                                                                                                 |
| METC    | Medical research ethics committee (MREC); in Dutch: medisch ethische toetsing commissie (METC)                                                                                                                                                                                                                                            |
| (S)AE   | Serious Adverse Event                                                                                                                                                                                                                                                                                                                     |
| SPC     | Summary of Product Characteristics (in Dutch: officiële productinformatie IB1-tekst)                                                                                                                                                                                                                                                      |
| Sponsor | The sponsor is the party that commissions the organisation or performance of the research, for example a pharmaceutical company, academic hospital, scientific organisation or investigator. A party that provides funding for a study but does not commission it is not regarded as the sponsor, but referred to as a subsidising party. |
| SUSAR   | Suspected Unexpected Serious Adverse Reaction                                                                                                                                                                                                                                                                                             |
| Wbp     | Personal Data Protection Act (in Dutch: Wet Bescherming Persoonsgegevens)                                                                                                                                                                                                                                                                 |
| WMO     | Medical Research Involving Human Subjects Act (Wet Medisch-wetenschappelijk Onderzoek met Mensen)                                                                                                                                                                                                                                         |

## SUMMARY

**Rationale:** Recent evidence indicates that individual daily life person-context interactions determine vulnerability for depression, and predict relapse as well as recovery. We hypothesize that momentary assessment technology (the MET-D device) to monitor these daily life person-context interactions during treatment will enrich passive antidepressant pharmacotherapy with an active resource-mobilising therapeutic context, thus enhancing therapeutic efficacy (reducing symptoms and relapse rate). Genetic factors play an important role in depression and sensitivity to stress and may therefore impact on the therapeutic efficacy of monitoring with MET-D.

**Objective:**

- (1) Does feedback on continuous monitoring with MET-D during pharmacotherapy result in a better treatment response (immediate and follow-up reductions of depressive symptoms, decreased relapse risk)?
- (2) Is feedback on continuous monitoring with MET-D during pharmacotherapy cost-effective?
- (3) Do measurements of daily life person-context interactions improve the prediction of future courses of depressive symptoms?
- (4) Can individual differences in (1) the effect of feedback on daily life person-context interaction and (2) the predictive value of these person-context interactions be traced back to genetic differences?

**Study design:** Randomized clinical trial with three groups of 40 subjects each (2 experimental groups and 1 control group). The first group receives a 5-day pre- and post MET-D assessment *and* a continuous MET-D assessment (3 days of MET-D measurements during a 6-weeks period) *with weekly feedback* (to both patient and therapist) during treatment as usual (TAU). The second group also receives a 5-day pre- and post MET-D assessment *and* a continuous MET-D assessment (3 days of MET-D measurements during a 6-weeks period) but *without feedback* during treatment as usual (TAU). The third group receives a 5-day pre- and post MET-D assessment but no additional intervention during TAU. This is the control group.

**Study population:** A sample of patients (n=120) with a depressive disorder will be recruited within (i) SEARCH, the research network of mental health institutions within Limburg and South-Brabant, The Netherlands, (ii) general practices and (iii) the general population.

**Intervention (if applicable):** The MET-D is a recently developed wearable interactive palmtop suitable for the Experienced Sampling Method (ESM) to study subjects in their daily life. The intervention group receives feedback on MET-D measurements of reward experience in daily life.

**Main study parameters/endpoints:** The rate of change in reward experience measured with the MET-D, and the change in depression symptomatology measured with the Structured Clinical Interview for DSM-IV Axis I Disorders (SCID-I) and the Hamilton Depression Rating

Scale (HDRS). Reward experience is conceptualised as the degree of positive affect following small positive daily events.

**Nature and extent of the burden and risks associated with participation, benefit and group relatedness:** There are no health risks associated with participation. Personal benefits for the subjects are (i) an increase in insight and control over recovery mechanisms, and (ii) the standard treatment can be adapted to the individual needs with the use of feedback. Burden for the patients is investment of time. After a screening procedure (3 hours), the time investment for subjects is approximately 5.5 hours comprising interviewing and self-report questionnaires (distributed over 7 meetings). In addition, all subjects have to participate twice in a 5-days MET-D measurement period (approximately 4 hours in total). Time investment for subjects in both experimental groups comprises an additional 13.5 hours. MET-D measurement takes place in the living environment of the patient, and as such reduces the burden for the patient.

## 1. INTRODUCTION AND RATIONALE

According to the World Health Organisation (WHO), depression is among the leading causes of disability worldwide, affecting about 121 million people worldwide of whom fewer than 25% have access to effective treatment. A disorder which is so prevalent conveys a very large burden on the health care system and results in large accompanying costs of health care and loss of productivity in the economic sector. In the Netherlands, depression has a life time prevalence of 15.4%, and a 12-month prevalence of 5.8% (NEMESIS-study) [1]. Residual symptoms after antidepressant therapy, relapse and treatment-resistance are often observed. The risk for chronicity is considerable (20%) [2].

Recently evidence is emerging that daily life person-context interactions not only determine vulnerability for depression [3], but also predict recovery [4] as well as relapse [5]. This creates an interesting window of opportunity, not only for the study of the etiology of depression, but also for the study of intervention possibilities. Daily person-context interactions involve the way a person reacts to his or her environment. For example, a telephone call with an unsatisfied client making you feel tensed for the rest of the day. Depression is associated with low positive affect (anhedonia) and with high negative affect. These are separate and independent affect dimensions [6]. The degree of positive affect following small positive daily events is known as the concept of 'reward experience'. Depressed persons experience a low level of reward during daily life. Reward experience is important because it can buffer negative affect in depressive subjects. One study showed that recovery in depression occurred in those with increases in the ability to experience reward from daily life situations during antidepressant treatment.

Furthermore, positive emotions in daily life make people more resilient against depression because it reduces the relapse rate for depressive episodes [5]. For example, a pilot study (n=61) was performed that examined whether affective response patterns in daily life influenced future relapse in individuals with a history of depression. The data showed that positive affective responses to pleasant events (reward experience) were an important predictor of future reduction in depressive symptoms and relapse. These studies indicate that (i) improvement of reward experience is likely to aid recovery and reduce future relapse and is thus an attractive target for the study of intervention possibilities and (ii) that information from individual affective responses to daily life contexts provides extra information that may help improved prediction of future course of depression.

In the field of depression a large number of studies examined the relationship between environmental stressors (such as negative life events) and the development of depressive symptoms [7]. Results suggest that although the existence of negative life events is an important risk factor in the development of depression, the existence of minor stressors in daily life may have an even larger effect due to its daily repetitive and possibly cumulative nature [8]. Daily

negative events result in the development of large amounts of negative affect which lead to a high risk for development of depressive symptoms [3]. The degree of negative affect following small negative daily events is known as 'stress sensitivity' [3]. Earlier studies have shown that stress sensitivity is an underlying mechanism with a genetic basis in the etiology of depression [3], and as such can be regarded as an endophenotype of depression [9].

The measurement of reward experience and stress sensitivity as operationalisations of daily person-context interactions creates an opportunity to zoom in on personal coping mechanisms, examining the way a subject interacts with his or her environment. This can on the one hand result in knowledge of the way a person enables his personal resources in coping with depressive symptoms, and on the other hand result in better monitoring compared to usual measures of treatment efficacy [10].

Measurement of daily person-context interactions must take place at those moments in which an individual interacts with his environment to provide ecologically valid information. The Experience Sampling Method (ESM) is suitable for this purpose [11-13]. Several studies of depression have been performed with the ESM paradigm, and this procedure is not only ecologically valid but proves to have a good validity and reliability [14-16]. The validity and reliability of ESM for the measurement of direct effects of daily stressors on mood has also been demonstrated [3, 11-13]. New technology to electronically monitor the patients' dynamic daily life responses to their personal context for extended periods (4-6 weeks) has recently become available and is patented by our group under the name 'MET-D device'. This device is not only suitable for ESM, but it can also electronically summarize the information of daily person-context interactions. This creates the possibility to provide feedback to subjects on their patterns of emotional responses to daily life situations. Receiving feedback on behavior can result in emotional and behavioral change, as is already known from the field of behavioral therapy [17-20]. Feedback on MET-D measurements of reward experience and affect variability may create an active and possibly therapeutic context for the depressed patient. Feedback can be given to both patient and therapist. For the patient, feedback can result in an increased insight in personal functioning, awareness of small improvements leading to more control over possible causes of depressed mood, and finally an increased use of the patient's personal resources. For the therapist, feedback can result in a better monitoring of both compliance and the effect of the treatment. The application of feedback on dynamic daily life person-context interactions, as measured with the MET-D, may improve therapeutic efficacy by means of enrichment of passive antidepressant pharmacotherapy with an active resource-mobilizing therapeutic context.

The aim of this study is to examine the therapeutic and predictive possibilities of the MET-D. We expect that (i) MET-D feedback on reward experience and affect variation enhances pharmacotherapeutic efficacy resulting in a better treatment response (immediate and follow-up

reductions of depressive symptoms and reductions in relapses) leading to a reduction in health care consumption and costs.

A second aim of this study is to evaluate whether the use of the MET-D, from the viewpoint of the society, is preferable compared to Usual Care in terms of effects (depressive symptoms, relapse), utilities (quality of life), and costs. Based on this main research question several sub-questions are relevant, such as: 1a) What are the (extra) costs of the delivery of MET-D (with and without feedback) compared to Usual Care? 1b) What are the (extra) effects (measured in depressive symptoms, relapse, and quality of life) of MET-D (with and without feedback) compared to Usual Care? We expect that (ii) MET-D feedback on reward experience and affect variation will be cost-effective.

Furthermore, we hope to confirm recent results regarding the role of reward experience, as described above, in the prediction of a depressive relapse [5]. We expect that (iii) the ability to generate reward experience predicts a decreased risk for the development of a depressive relapse. MET-D measurement of reward experience may thus lead to an improvement of the prediction of future courses of depressive symptoms.

Not only person-context interactions, as measured with the MET-D, are important in the etiology of depression and in the prediction of future depressive episodes. Evidence on the important role of genetic influences on both depression as well as on stress sensitivity is emerging [3, 21-27]. For example, subjects who are 'Met' carriers of the BDNF gene exhibit increased stress sensitivity compared to the 'Val/Val' carriers [28]. Since stress sensitivity influences treatment response [4], it can be hypothesized that treatment effect may be partly under genetic control, as is demonstrated by recent findings [29]. This may be due to the intermediate action of stress sensitivity. Therefore, our final goal is (iiii) to examine the influence of genetic differences on both the effect of MET-D feedback on treatment response, and on the predictive value of daily life person-context interactions on relapse risk.

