#### Design:

A randomized controlled trial will be conducted with three treatment arms:

- The **first** arm ('MET-D intervention *with* feedback'; n=40) receives 5-day pre- and post MET-D assessment *and* continuous MET-D assessment (each week 3-days MET-D measurement during a 6- weeks period) *with feedback* (to both patient and therapist) during treatment as usual (TAU= antidepressant pharmacotherapy). This is the experimental group.
- The **second** arm ('MET-D intervention *without* feedback'; n=40) also receives a 5-day pre- and post MET-D assessment *and* a continuous MET-D assessment (3 days of MET-D measurements during a 6-weeks period) but *without feedback* during treatment as usual (TAU). In order to prevent any effects of different duration of the weekly contacts with the researcher, alternative weekly activities (interviews on anxiety and depression) are carried out. This is the control experimental group.

- The **third** arm (control group; n= 40) receives 5-day pre- and post MET-D assessment but no additional intervention during TAU.

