For the economic evaluation, the Incremental cost-effectiveness ratio (ICER) will be determined on the basis of incremental costs and effects of MET-D (with and without feedback) compared Usual Care. The cost-effectiveness ratio will be stated in terms of costs per outcome rate, the cost-utility ratio will focus on the net cost per QALY gained. The ICER will be calculated as follows.  $ICER = (C_i - C_c) / (E_i - E_c)$ , where  $C_i$  is the annual total cost of the MET-D (with and without feedback) group,  $C_c$  is the annual total cost of the Usual Care group,  $E_i$  is the effects at one year follow-up for the MET-D (with and without feedback) group and  $E_c$  is the effect at one year follow-up for the Usual Care group. The robustness of the ICER will be checked by non-parametric bootstrapping (1000 times) [47]. Bootstrap simulations will also be conducted in order to quantify the uncertainty around the ICER, yielding information about the joint distribution of cost and effect differences. The bootstrapped cost-effectiveness ratios will be subsequently plotted in a cost-effectiveness plane, in which the vertical line reflects the difference in costs and the horizontal line reflects the difference in effectiveness. The choice of treatment depends on the maximum amount of money that society is prepared to pay for a gain in effectiveness, which is called the ceiling ratio. Therefore, the bootstrapped ICERs will also be depicted in a cost-effectiveness acceptability curve showing the probability that MET-D (with and without feedback) is cost-effective using a range of ceiling ratios. Additionally, to demonstrate the robustness of our base-case findings a multi-way sensitivity analyses will be performed. In the sensitivity analysis uncertain factors of assumptions in the base case analysis will be recalculated in order to assess whether the assumptions have influenced the incremental cost-effectiveness ratio (ICER), for example by varying cost-prices and volumes between minimum and maximum [47].

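### The economic sub-questions and the ICER label arm 2 versus arm 3 as MET-D without feedback against Usual Care, but arm 2 is a package that also contains weekly researcher sessions and twelve filler interviews

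*Protocol*

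**What the plan says.** **The comparison.** Section 1 splits the economic aim into a cost question, "What are the (extra) costs of the delivery of MET-D (with and without feedback) compared to Usual Care", and an effects question, "What are the (extra) effects (measured in depressive symptoms, relapse, and quality of life) of MET-D (with and without feedback) compared to Usual Care". Section 9.2 repeats the comparison: the ICER is to be formed "on the basis of incremental costs and effects of MET-D (with and without feedback) compared Usual Care". The acceptability curve is described as "showing the probability that MET-D (with and without feedback) is cost-effective using a range of ceiling ratios".

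**The arms.** Section 3 (Design) gives arm 2 six weeks of MET-D without feedback and adds: "In order to prevent any effects of different duration of the weekly contacts with the researcher, alternative weekly activities (interviews on anxiety and depression". Section 3 (Feedback) and section 7.3 put this at two more interviews each week. Section 3 (Feedback) also says that arms 1 and 2 both meet the researcher weekly, with a debriefing on the MET-D recordings. Arm 3 "receives 5-day pre- and post MET-D assessment but no additional intervention during TAU".

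**The hypothesis.** The Summary rationale speaks of monitoring: it expects that "momentary assessment technology (the MET-D device) to monitor these daily life person-context interactions during treatment will enrich passive antidepressant pharmacotherapy". Objectives 1 and 2 in section 2, and the expectations in section 1 about efficacy and cost-effectiveness, speak of feedback.

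**The role of arm 2.** The Summary counts arm 2 among two experimental groups. Section 3 calls it the control experimental group. Section 10.4 refers to control conditions in the plural, which must include it.

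**The concern.** The protocol accepts that time spent with the researcher may itself change the outcome, and equalises that time between arms 1 and 2 for this reason. It does not do so between arms 2 and 3, yet the economic plan names the difference between those two arms after the device. The filler interviews also deal with anxiety and depression, so they touch the outcome domain directly.

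Arm 2 is a sensible attention control for feedback. The difficulty starts when the same arm is used as a candidate strategy with its own effect and its own ICER. If weekly contact or repeated interviewing changes depressive symptoms, relapse or quality of life, that change would be reported as an effect, and as the cost-effectiveness, of MET-D monitoring. Costs are among the main outcomes in section 7.1.1, so the label matters.

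**Working it through.** **1. Content of the six-week period** (sections 3 and 7.3)

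| Component | Arm 1 | Arm 2 | Arm 3 |
|---|---|---|---|
| Usual treatment | yes | yes | yes |
| MET-D, 3 days × 6 weeks = 18 days | yes | yes | no |
| Weekly researcher session with MET-D debriefing, 1 × 6 = 6 | yes | yes | no |
| Feedback to patient and therapist, 6 times | yes | no | no |
| Extra anxiety/depression interviews, 2 × 6 = 12 | no | yes | no |

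**2. What each contrast contains.** Write m for the MET-D recordings, s for the sessions with debriefing, f for the feedback part of the session and i for the filler interviews. For illustration, assume that the effects add.

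- Arm 2 − arm 3 = m + s + i
- Arm 1 − arm 2 = f − i, which is feedback against equal contact time
- Arm 1 − arm 3 = m + s + f
- Pooled arms 1 and 2 (40 each) − arm 3 = m + s + (f + i)/2

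No contrast yields m alone. The filler term i enters arm 2 versus arm 3 in full. If the phrase about with and without feedback means one pooled group, it enters with weight one half. In arm 1 versus arm 2 it does the job it was designed for.

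**3. Time, for orientation only.** Section 10.4 puts the extra burden of arms 1 and 2 at 13.5 h. There are 18 × 10 = 180 signals.

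- At 30 s per signal (section 3): 180 × 30 s = 1.5 h, leaving 13.5 − 1.5 = 12.0 h.
- At 4 h per 10 days (section 10.4): 18 × 0.4 h = 7.2 h, leaving 13.5 − 7.2 = 6.3 h.

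So 6.3 to 12.0 h are not spent answering signals. This remainder mixes the filler interviews with the debriefing and the SCL-90 items entered each evening on the device. The length of the interviews is not stated, so their share cannot be worked out.

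**4. Effect size.** The protocol gives no effect of contact and no SD. Section 4.4 reports a power of 0.93 for 3 HDRS-17 points. This cannot be reproduced without the SD, and the present point does not depend on it.

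**5. Cost side.** Section 9.2 defines C_i as the yearly total cost of the MET-D group and E_i as the effect in that same group. Read literally, both terms cover the whole package. No section says explicitly whether the sessions and the filler interviews are costed.

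**6. Objective 2.** It asks whether feedback is cost-effective. Section 9.2 specifies an ICER against Usual Care only and names no arm 1 versus arm 2 increment.

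**The case against.** Four arguments speak against the concern.

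- **A package comparison is legitimate.** From a societal viewpoint, a randomised comparison of a strategy with Usual Care is a proper question, and section 3 discloses what arm 2 receives. This stands: the contrast is unbiased for the package. It does not justify giving the result the name of one component.
- **The main claims concern feedback.** Objectives 1 and 2 and the stated expectations name feedback, which arm 1 versus arm 2 tests with matched contact. This stands, and it limits the point to the economic sub-questions. The Summary's sentence on monitoring is thin support for a monitoring-alone hypothesis and need not be rewritten.
- **The debriefing belongs to MET-D.** It deals with missed entries, technical problems and unclear items, so it can reasonably count as delivery of MET-D. This largely stands for the sessions. It does not carry over to the twelve interviews, whose only stated purpose is to fill time.
- **Costing detail may be in another document.** That is fair for unit prices and volumes. The contrast, its label and the reading of the acceptability curve, however, are fixed in the protocol.

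A reader might also infer that the ICER sets the cost of the device against the effect of the whole package. The definitions of C_i and E_i in section 9.2 do not support that, since both refer to the same group.

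**Conclusion.** The point holds as one of labelling and attribution. Arm 2 versus arm 3 estimates the effect and cost of MET-D monitoring plus weekly researcher contact and twelve interviews, against Usual Care. Followed as worded, the plan would credit any contact effect to MET-D without feedback. The known size is the content of the difference: 6 sessions, of which the debriefing may belong to MET-D, and 12 interviews, which do not. The effect of that content is unknown in size and direction, so no bias of a given amount is shown.

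Two stronger readings go beyond the documents:

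- **That most of what separates arms 2 and 3 is not MET-D.** The hours do not show this, because the debriefing and the evening items fall in the remainder and because minutes do not measure exposure to signals spread over 18 days.
- **That the test of arm 2 versus arm 3 has an inflated error rate.** If contact works, the package does differ from Usual Care, and detecting this is power. Any probability put on it would need an assumed contact effect and an assumed SD.

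The feedback contrast, arm 1 versus arm 2, is unaffected.

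**What to change.** In section 1 (sub-questions 1a and 1b) and section 9.2:

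1. Describe the arm 2 strategy as MET-D monitoring plus weekly researcher sessions and interviews. State that effects or an ICER from arm 2 versus arm 3 will not be interpreted as those of MET-D monitoring alone. Say whether arms 1 and 2 are compared with Usual Care separately or pooled; if pooled, the same caution applies.
2. State that C_i for arm 2 includes the researcher sessions and the filler interviews, in line with the existing definition of C_i as the total cost of the group that supplies E_i. Add a sensitivity analysis that leaves out the interview cost.
3. For objective 2, also report the incremental costs and effects of arm 1 versus arm 2. Show this with and without the interview cost, because costing the filler in arm 2 lowers the apparent extra cost of feedback.

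The package contrast can still be reported as such; no ban on claims from it is needed. The change costs some wording, one costing statement and one further economic comparison on data already planned, with no new patients or measurements. The downside is that the sponsor gives up a claim about monitoring alone, and that the arm 2 ICER may look less favourable.
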